### Prespecified subgroup analysis

2.12

A subgroup analysis will be performed on the use of antibiotics and no antibiotics in the TCM and placebo groups to explore the correlation between antibiotic therapy and the outcomes of the study.

### Safety assessment

2.13

During the hospital stay, the patient will receive a daily physical examination and report to the bed physician for the recording of the symptoms and more or worse comorbidities to detect and deal with possible adverse reactions in a timely manner. Before treatment, during treatment, and on discharge, blood routine, urine routine, liver and kidney function, electrolytes, electrocardiogram (ECG), pulmonary function, blood gas analysis, and other inspections will be performed to assess whether there are adverse reactions related to treatment.

### Study procedures

2.14

Eligible subjects will be screened 2 days before the trial. Randomized group treatment will be conducted after informed consent is obtained and baseline information is collected. The duration of the intervention will be the entire hospital stay (7–14 days). All hospitalized patients will complete the CAT, mMRC, and 6MWD scales every day. The physician should record each patient's glucocorticoid dosage every day and make corresponding adjustments according to the CAT scores. The patients will be asked about their symptoms and quality of life scores (assessed by CAT, mMRC, and 6MWD) after discharge for 12 weeks by weekly telephone follow-up. The spirit figure of enrollments, interventions, and assessments is presented in Figure 2.^[15]^

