### Sample size

2.5

Based on the primary endpoint (the dosage of systemic glucocorticoids) to calculate sample size. According to a previous study,^[17]^ the dosage of systemic glucocorticoids during the hospitalization of patients with AECOPD with TCM is 187.6 ± 31.1 mg (methylprednisolone sodium succinate for injection) and that with western medicine treatment is 256.7 ± 32.9 mg. Using a formula, we will set α = 0.05 and β = 0.2 and hope that 80% power can be used to uncover the true difference between the treatment options. According to the formula, nc = (μ1−α / 2 + μ1−β) ^2^S^2^ (1 + 1 / k) / (μt-μc) 2 = 87. Thus, the control group requires 87 cases. According to the 1:1 ratio, a total of 174 cases are needed in the two groups. Considering a possible dropout rate of 15%, a total of 174/0.85 = 204 cases are required, with 102 cases in each group.

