### Randomization and intervention

2.6

The randomization protocol will be designed by a member of the Sichuan TCM Evidenced-Based Medicine Center. They will generate 204 random numbers will using SAS 9.2 statistical software (SAS Institute, Cary, NC). Treatment allocation will be conducted by an independent statistician according to the random numbers generated by the statistical software. Eligible patients will be randomly assigned to either the TCM group or the placebo group using sealed opaque envelops after obtaining informed consent. A special manager will record this randomization process. An individual's randomization number and group allocation can be identified by checking the envelope, which will be performed in case of a clinical emergency.

All participants will receive basic Western medical therapy advocated by the Chinese Expert Consensus on the diagnosis and treatment of AECOPD (2017 update),^[8]^ which includes:

1.Controlled oxygen therapy: Venturi mask inhales oxygen.2.Bronchodilators: compound ipratropium bromide solution for inhalation (Laboratoire Unither, Amiens, France), 2.5 mL, inhale, three times a day;3.Phlegm medicine: fudosteine tablets (Pharmaceutical Co., Ltd.), 0.4 mg, orally, three times a day;4.Glucocorticoids: methylprednisolone sodium succinate for injection (Tianjing Jinyao Pharmaceutical Co., Ltd. Tianjing, China), 40 mg, administered with 0.9% sodium chloride injection (100 mL), intravenously, once a day (depending on the patient's condition, the dosage can be reduced or changed to oral administration, but the longest course of treatment cannot exceed 14 days);5.Antibacterial drugs: according to bacterial resistance and the general course of treatment will be 5 to 7 days, although special circumstances can appropriately extend the application time of antibacterial drugs.

In addition, the TCM group will receive TCM granules (one bag at a time, three times a day) and the Placebo group will receive Placebo granules (one bag at a time, three times a day). Both groups will or will not receive antibiotic treatment according to the antibiotic treatment criteria, which are:

1.During AECOPD, aggravated difficulty breathing, increased sputum volume, and purulent sputum occur simultaneously;2.The patient only has two of the above three symptoms, but has purulent sputum;3.Severe acute exacerbation that requires invasive or noninvasive mechanical ventilation.

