### Follow up

2.9

Patients will be followed up by phone once a week for 12 weeks after discharge. The contents of the follow up mainly included the scores of CAT, mMRC, and 6MWD.

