### Primary outcome measure

2.10

**The dosage of systemic glucocorticoids (at which the CAT scores improve by 50%)**. Measurement methods: ([admission CAT scores − post-intervention CAT scores)/admission CAT scores) × 100%. Record glucocorticoids dosage in case report form (CRF) based on CAT scores.

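### The dose window of the primary outcome is defined inconsistently and can be cut off at discharge, so an arm that goes home earlier can look steroid-sparing or leave patients without a value

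*Protocol article*

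**What the plan says.** The protocol article describes the primary outcome in several places that do not agree on when the counting of dose stops.

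- **Sections 2.1 and 2.10** define it as "The dosage of systemic glucocorticoids (at which the CAT scores improve by 50" per cent. Improvement is the percentage fall from the admission CAT score.
- **Section 2.5** sizes the trial on a different quantity: "the dosage of systemic glucocorticoids during the hospitalization of patients with AECOPD with TCM is 187.6 ± 31.1 mg", against 256.7 ± 32.9 mg under western treatment. This is dose over the stay, with no CAT threshold.
- **Section 2.14** has the physician record each patient's "glucocorticoid dosage every day and make corresponding adjustments according to the CAT scores". The sentence stands between the daily scales for inpatients and the telephone follow-up.

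The surrounding rules are these.

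- **Section 2.6:** methylprednisolone 40 mg intravenously once a day; "the dosage can be reduced or changed to oral administration, but the longest course of treatment cannot exceed 14 days".
- **Sections 2.7 and 2.14:** the stay, which is also the intervention period, is 7 to 14 days.
- **Section 2.8:** eight discharge criteria. None asks that the systemic steroid course be finished, and none refers to CAT.
- **Section 2.9:** "The contents of the follow up mainly included the scores of CAT, mMRC, and 6MWD". Sections 2.11 and 2.14 name the same three measures for the calls.
- **Section 2.11:** length of stay is a secondary efficacy outcome.

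**The concern.** If dose is counted over the hospital stay, the observation period ends at discharge. Discharge happens after randomisation, and the trial itself treats its timing as something TCM may change. Steroid taken at home would then drop out of the primary outcome, and more of it would drop out in the arm that leaves sooner.

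If dose is counted to a 50% CAT improvement, the difficulty moves to patients who go home before reaching it. Their CAT is still collected weekly by telephone, but no dose is described as being collected with it.

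The Introduction and Discussion justify the trial by steroid harm that rises with dose. That harm follows what the patient takes, not what was charted before discharge.

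**Working it through.** **1. The plan's own figures (section 2.5).** Difference: 256.7 − 187.6 = 69.1 mg. Pooled SD: √((31.1² + 32.9²)/2) = 32.0 mg. The stated formula gives 2 × (1.96 + 0.84)² × 32.0² / 69.1² = 3.4, so 4 per arm, not the stated 87. To reach 87 the SD would have to be 69.1 × √(87/2) / 2.80 = 162.7 mg. That mismatch is a separate problem. It matters here only because it leaves the SD in doubt, so both values are used in step 5.

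**2. Can an allowed course outlast the stay?** The longest course is 14 days and the shortest stay 7, so up to 14 − 7 = 7 days can fall after discharge. At 40 mg/day that is 7 × 40 = 280 mg for one patient. This is a ceiling, not an estimate: it exceeds the control arm's whole cited mean of 256.7 mg.

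**3. The two readings side by side** (the threshold dose is taken as cumulative dose up to the threshold).

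| Patient | In-hospital dose (2.5) | Dose to 50% CAT improvement (2.1, 2.10) |
|---|---|---|
| Reaches 50% in hospital, steroid finished before discharge | Complete | Determined |
| Reaches 50% in hospital, leaves on steroid | Cut off at discharge | Determined; later steroid does not count |
| Leaves before 50%, on steroid | Cut off at discharge | Not determinable from what is described |
| Leaves before 50%, steroid finished | Complete unless restarted | No value assigned |

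**4. Would patients be on steroid at discharge?** The planned difference is 69.1/40 = 1.73 days at 40 mg. The cited means are 187.6/40 = 4.7 days (TCM) and 256.7/40 = 6.4 days (control), both under the 7-day minimum stay. Under a normal distribution, the share above 280 mg (7 days at 40 mg) is 1 − Φ((280 − 187.6)/31.1) = 0.1% for TCM and 1 − Φ((280 − 256.7)/32.9) = 24% for control. So at a constant 40 mg/day most courses would end before the earliest discharge. Section 2.6 allows reduction, though. At an assumed 20 mg/day, used for arithmetic only, the same totals last 187.6/20 = 9.4 and 256.7/20 = 12.8 days, within the range of the stay.

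**5. Illustration on the in-hospital reading.** Assume no true difference in total dose, discharge one day earlier in one arm, and 87 patients per arm. Spurious difference = daily dose × 1 day × share still on steroid at discharge. The chance of a significant result favouring the earlier-discharged arm is Φ(difference/SE − 1.96), with SE = SD × √(2/87): 4.85 mg at SD 32.0 and 24.7 mg at SD 162.7. Without bias that chance is 2.5%.

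| Daily dose, share on steroid | Spurious difference | SD 32.0 | SD 162.7 |
|---|---|---|---|
| 20 mg, 25% | 5 mg | 18% | 4% |
| 20 mg, 50%, or 40 mg, 25% | 10 mg | 54% | 6% |
| 20 mg, 100%, or 40 mg, 50% | 20 mg | 98% | 13% |
| 40 mg, 100% | 40 mg | >99% | 37% |

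The one-day gap and the shares are assumptions; the document gives neither.

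**The case against.** The strongest reply is that sections 2.1 and 2.10 define the outcome by the CAT threshold. For a patient who reaches it in hospital, later steroid does not enter the outcome, and earlier discharge cannot lower the value. This stands. A reader might infer that a shorter stay lowers the recorded dose as a matter of course. The document does not support that: it follows only on the in-hospital reading, and only for patients who leave on steroid or restart it.

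A reader might also price the bias by assuming 40 mg on every inpatient day. The minimum stay alone would then give 280 mg, above both cited means, so that scenario does not fit section 2.5.

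Third, a reader might infer that post-discharge steroid is certainly not collected. The article is condensed, section 2.9 qualifies its list with *mainly*, and the schedule in Figure 2 is not shown. What can be said is that the content of the calls is given three times and steroid use is not named.

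Last, it might be inferred that leaving out steroid for relapse over the 12 weeks is an error. The Discussion limits the aim to dose in hospitalized patients, so it is not.

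None of this removes the conflict between sections 2.5 and 2.10, or supplies a value for a patient discharged below the threshold.

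**Conclusion.** The point holds as an inconsistency in the primary outcome with a conditional bias attached. The dose window differs between the definition and the sample size, recording is described as an inpatient procedure, and discharge is tied neither to the end of the course nor to the threshold.

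The direction of the bias is clear where it occurs: on the in-hospital reading it favours the arm discharged earlier. It needs two things together, steroid continuing or restarting after discharge and a difference between arms in discharge timing. On the threshold reading the problem is undefined values, whose number and balance between arms are unknown.

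The size cannot be derived from the document. It depends on how many patients leave on reduced or oral dosing, on the gap in discharge timing and on the SD. The illustrations range from negligible to enough for a false claim. It should be settled before recruitment, because doses not collected cannot be recovered in the analysis.

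**What to change.** 1. Reconcile the dose window across sections 2.1, 2.5, 2.10 and 2.14, so that the outcome defined, sized and recorded is the same quantity.
2. Record systemic glucocorticoid use, intravenous plus oral in methylprednisolone equivalents, for every patient from randomisation to day 14, whatever the discharge date. Fourteen days is the protocol's own maximum course. The first weekly calls already planned can cover the days at home.
3. State how a patient discharged before a 50% CAT improvement is counted in the primary analysis.
4. Report the fixed-window cumulative dose alongside the CAT-threshold endpoint, at least as a prespecified sensitivity analysis. Making it the primary endpoint would change the question the trial asks and should be an open decision, not a by-product of this correction.
5. Optionally, ask about steroid for relapse on the remaining calls as supportive information.

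The change concerns measurement and definition only and leaves treatment as it is. It costs a few questions on existing calls, a case report form field and a clarified definition. The drawback is some recall error for doses taken at home.

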**Figure 2 F2:**
[figure not shown]
Spirit figure of enrollment, interventions, and assessments.^[15]^6MWT = 6-minute walk test, CAT = COPD assessment test, CRP = C-reactive protein, FEV1 = forced expiratory volume in 1 second, FEV1/FVC = the ratio of forced expiratory volume in 1 second to forced vital capacity, FEV1% = FEV1 as a percentage of expected value, FVC = forced vital capacity, mMRC = modified medical research council dyspnea scale scores, PCT = procalcitonin;TCM = traditional Chinese medicine, WBT = western basic therapy.

### Quality control and data management

2.15

The study protocol has been reviewed and revised several times by the principal scientists of this protocol. To ensure that all members of the study are familiar with the study procedures and rules to ensure that the study is completed successfully, they will be required to take part in a series of training. All data will be collected by a trained and qualified investigator and recorded in CRF. To ensure the authenticity of the data, the original record will not be changed if any corrections are made once a CRF is completed.

The entire process of data entry and management will be monitored by a designated researcher. The established data will be locked by the main data managers and statistical analysts after reviewing and confirming that the data are correct. Any problems encountered after the data are locked can be corrected in the statistical analysis program after confirmation. Data audits in the middle of the trial will be performed independently by an investigator from the Department of Science Research of the Affiliated Hospital of Chengdu University of Traditional Chinese Medicine.

### Statistical analysis

2.16

Intention-to-treat analysis and per-protocol analysis will be used. Intent-to-treat analysis means that after subjects are randomized, whether they choose to withdraw from the trial or switch to another group, their results are based on their initial grouping during data analysis. Intention-to-treat analysis will be used to analyze completed cases and dropout cases. Efficacy analysis adopts per-protocol analysis; thus, it kicks out those cases with insufficient compliance during the analysis and analyzes only the completed cases. When there is a difference between the two results, the difference will be discussed and explained.

We will use SPSS 19.0 statistical software for statistical analysis. The measured value of the data will be expressed as mean ± standard deviation. If the data follow the normal distribution and the variance is homogeneous, the *t* test will be used; however, if the data does not follow the normal distribution or the variance is uneven, the Wilcoxon rank-sum test will be sued. The Bonferroni method will be used to further compare the differences between antibiotic and non-antibiotic subgroups to explore whether antibiotics will affect the outcomes. The Chi-square test will be used for counting data and rank-sum test will be used for ranking data. All tests will be two-sided, with *P* < .05 being considered statistically significant.

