### Trial design and oversight

2.1

This will be a prospective, placebo-controlled clinical trial to evaluate the efficacy of TCM in the treatment of patients with AECOPD. A total of 204 eligible patients will be enrolled according to the exclusion and inclusion criteria and randomly assigned to the TCM or placebo group at a 1:1 ratio. The antibiotic group and non-antibiotic group will be set in advance for subgroup analysis. After a 7–14 day intervention and 12 weeks of follow up, the efficacy of TCM in the treatment of patients with AECOPD will be evaluated based on the primary endpoint (the dosage of systemic glucocorticoids [at which CAT scores improve by 50%]) and secondary endpoints (symptoms scores, exercise tolerance, lung function, length of hospital stay, symptoms, and quality of life scores during the follow up). The flow chart of the study is presented in Figure 1.

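### Efficacy is assigned to per-protocol completers, and the planned intention-to-treat analysis is given no deciding role

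*Protocol article*

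**What the plan says.** The Statistical analysis section (2.16) opens by planning both sets: "Intention-to-treat analysis and per-protocol analysis will be used". It defines ITT properly, by initial group whether or not a patient withdraws or switches, and adds: "Intention-to-treat analysis will be used to analyze completed cases and dropout cases".

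It then names the set that answers the efficacy question: "Efficacy analysis adopts per-protocol analysis; thus, it kicks out those cases with insufficient compliance during the analysis and analyzes only the completed cases". The only rule for disagreement is: "When there is a difference between the two results, the difference will be discussed and explained".

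The purpose is stated under Trial design and oversight: "This will be a prospective, placebo-controlled clinical trial to evaluate the efficacy of TCM in the treatment of patients with AECOPD". Allocation is 1:1, tests are two-sided at the 5% level, and no non-inferiority margin appears anywhere. No section that deals with the primary endpoint (Trial design and oversight, Sample size, Primary outcome measure, Discussion) gives ITT precedence for the steroid dosage.

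**The concern.** In a superiority comparison, randomisation supports the inference only if the groups compared are the groups randomised. Poor compliance and non-completion both arise after allocation, and both may be related to how the patient is doing.

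The endpoint makes this more than a formality. Under Study procedures, the physician adjusts the steroid dose according to daily CAT scores, and the primary outcome is the dosage at which CAT has improved by 50%. Patients who do badly, cannot tolerate the granules or leave early may therefore differ in steroid need from those who stay. That link is a reasonable inference; the article does not state it. If more such patients are removed from the TCM arm than from the placebo arm, an apparent steroid saving appears without any drug effect. If the imbalance runs the other way, a real saving is masked.

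At stake is which patients count in the trial's main claim. The article makes a positive choice here, so this is not a detail left to an analysis plan. An unseen plan that made ITT primary would contradict this sentence.

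**Working it through.** **Inputs from the article (Sample size)**
- TCM arm: "with TCM is 187.6 ± 31.1 mg". Western medicine arm: 256.7 ± 32.9 mg. Difference 256.7 − 187.6 = 69.1 mg.
- Pooled SD = √((31.1² + 32.9²)/2) = √1024.8 = 32.0 mg.
- "we will set α = 0.05 and β = 0.2"; 87 per arm before dropout; 15% dropout; 204 in total, 102 per arm.

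**The plan's own figures.** 174/0.85 = 204.7, which agrees with the stated 204 to within rounding up. Fifteen per cent of 204 is 30.6, so the plan itself expects about 31 patients to drop out. The 87 per arm does not follow from the stated means and SDs, which give 2 × (1.96 + 0.84)² × 1024.8/69.1² = 3.4, that is 4 per arm. That is a separate matter, and nothing below depends on it.

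**Assumptions, not in the article.** No drug effect; normal doses with SD 32 mg; 102 per arm; exclusion averaging 15% over the two arms. A latent exclusion score has correlation ρ with steroid need, and patients with the highest scores are removed. The larger exclusion is placed in the TCM arm.

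**Formula.** If a fraction f is removed, let c be the normal quantile at 1 − f and λ = φ(c)/(1 − f). The mean among those kept falls by ρ × λ × SD, and their variance is SD² × [1 − ρ²(cλ + λ²)]. The values of λ are 0.109 (5%), 0.195 (10%), 0.274 (15%), 0.350 (20%) and 0.424 (25%).

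- 15%/15%: the shifts cancel, so there is no bias.
- 20%/10%: spurious saving = ρ × (0.350 − 0.195) × 32 = 4.96ρ mg, or 1.5, 2.5 and 4.0 mg at ρ = 0.3, 0.5 and 0.8.
- 25%/5%: spurious saving = ρ × (0.424 − 0.109) × 32 = 10.1ρ mg, or 3.0, 5.0 and 8.1 mg.

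**One case by hand (20%/10%, ρ = 0.8).** Variance factors are 1 − 0.64 × 0.417 = 0.733 (TCM) and 1 − 0.64 × 0.288 = 0.816 (placebo). With 81.6 and 91.8 patients kept, SE = 32 × √(0.733/81.6 + 0.816/91.8) = 4.28 mg, and z = 3.97/4.28 = 0.93. Two-sided rejection ≈ Φ(0.93 − 1.96) + Φ(−0.93 − 1.96) ≈ 0.15.

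**Simulated type I error of the per-protocol t test (20,000 trials per cell)**

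| Excluded, TCM/placebo | ρ = 0 | ρ = 0.3 | ρ = 0.5 | ρ = 0.8 |
|---|---|---|---|---|
| 15%/15% | 5.0% | 5.1% | 5.0% | 5.0% |
| 20%/10% | 5.1% | 6.2% | 8.3% | 14.6% |
| 25%/5% | 5.2% | 9.4% | 18.2% | 45.1% |

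ITT on all 204 patients, with complete outcomes, stayed between 4.7% and 5.2% throughout.

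**The case against.** The best defence is that ITT is not absent. It is planned, correctly defined and set beside the per-protocol result, so a reader would see a positive per-protocol finding that ITT did not support. This stands, and it limits the point to precedence: the analysis that is reported but does not decide is the one that keeps the randomised comparison.

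It is also fair that differential exclusion is not certain. Treatment lasts only the inpatient stay of about 7 to 14 days, the placebo is made as close as possible in appearance and taste, and dosage is recorded daily. These features limit non-compliance that differs by arm, but they do not rule it out. The precise criteria for the per-protocol set may also sit in a fuller document and are not criticised here.

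Four stronger readings are tempting and are not supported:
- That the per-protocol analysis fails to hold 5% as such. It holds when exclusion is unrelated to steroid need, or when it acts equally in both arms.
- That the plan permits choosing the more favourable result. It says that differences will be explained; it states no such licence. What is missing is a rule saying which result decides.
- That the 69.1 mg treatment difference can stand for the dose gap between excluded and retained patients, which would suggest a very high false-positive rate. Nothing in the article links the two. With a normal outcome and SD 32 mg, removing exactly the highest 15% gives a gap of at most 1.83 × 32 = 58.5 mg.
- That all exclusions would fall in one arm. A 30%/0% split gives 16.4% to 79.3% in the same simulation, but nothing in the article points to so extreme an imbalance.

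**Conclusion.** The point holds as one of precedence. The article assigns efficacy to compliant completers and does not let ITT decide the conclusion, in a trial whose design implies superiority. Superiority is inferred from the placebo control, the two-sided tests and the absence of a margin.

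The harm is conditional: exclusion must both relate to steroid need and differ between arms. At the plan's own 15% average, the per-protocol type I error then runs from about 5% (balanced), through 6% to 15% (20%/10%), to 9% to 45% (25%/5%). The article gives only the 15%; the splits, the correlations and the normal model are assumptions. The matter should be settled before unblinded data are seen.

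**What to change.** In the Statistical analysis section, replace the sentence that assigns efficacy to the per-protocol set, and the sentence on differing results, with text to this effect:

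- The primary efficacy analysis is ITT: all randomised patients in their assigned group, using the in-hospital steroid record whether or not the granules were continued, in wording matched to the definition under Primary outcome measure.
- The efficacy conclusion rests on the ITT result.
- The per-protocol analysis is a supportive sensitivity analysis, and any difference from ITT is described.

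The cost is a few sentences and the approval that the article requires for any amendment. No new data item is needed: Study procedures already has the physician record each inpatient's steroid dosage daily, so recording has only to continue after granules stop. There is no meaningful loss of power on the plan's own inputs. With 102 per arm, 69.1/(32 × √(2/102)) = 15.4 standard errors, so power is above 99.9%.

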### Secondary outcome measure

2.11

**Symptoms scores**. Measured by CAT and mMRC scores. Patients will be required to complete assessments every day during hospitalization.

**Lung function**. Lung function indicators include FEV1, FEV1/FVC, and FEV1%. These will be compared before and after treatment.

**Exercise tolerance**. We will assess each patient's exercise endurance using 6MWD. Method: hospitalized patients will be asked to walk as far as possible within 6 min along flat ground once a day. For the standardized instructions of 6MWD, we will refer to the official European Respiratory Society/American Thoracic Society technical standard for field walking tests in chronic respiratory disease.^[18]^

**Inflammatory indicators**. Include CRP and PCT. We will collect the results of CRP and PCT in admissions and discharges.

**Length of hospital stay** Length of hospital stay = discharge date – admission date + 1.

**Symptoms and quality of life scores during the follow up.** Patients will be followed up by phone every week to produce the CAT, mMRC, and 6MWD scores for 12 weeks after discharge.

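### The data-driven switch from t test to Wilcoxon does not deal with unequal variance and leaves open whether mean dose or ranks are tested

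*Protocol article*

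**What the plan says.** Section 2.16 (Statistical analysis) of the protocol article sets one rule for measured data. The t test applies when the data are normal and the variances equal; otherwise "if the data does not follow the normal distribution or the variance is uneven, the Wilcoxon rank-sum test will be sued". Non-normality and unequal variance therefore lead to the same test. "All tests will be two-sided", at P < .05, and measured values are summarised as mean ± SD. No check of normality or variance is named.

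The primary endpoint is a dose in milligrams (2.10). The sample size (2.5) rests on two mean doses from a previous study: "the dosage of systemic glucocorticoids during the hospitalization of patients with AECOPD with TCM is 187.6 ± 31.1 mg" and "that with western medicine treatment is 256.7 ± 32.9 mg". Patients are "randomly assigned to the TCM or placebo group at a 1:1 ratio" (2.1).

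Baseline and repeated values are collected. CAT is taken at admission and enters the definition of the primary endpoint (2.10). Of the lung function measures, 2.11 says "These will be compared before and after treatment". CRP and PCT are taken at admission and discharge. In 2.14, "All hospitalized patients will complete the CAT, mMRC, and 6MWD scales every day", and weekly telephone calls follow for 12 weeks.

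**The concern.** There are two faults in the rule.

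- **Wrong remedy.** As a comparison of location, the rank-sum test needs the two distributions to have the same shape and spread. When spreads differ, it can reject although the mean doses are equal, most of all when the data are also skewed. Unequal variance calls for a test that allows for it, such as Welch's.
- **Shifting question.** The trial asks how much steroid is saved, and the sample size and the summaries are in mean mg. Under the Wilcoxon branch, the P value printed beside those means does not test them. Which question is answered is settled only once the data are seen.

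The Wilcoxon branch is a plausible path for the primary test. Under 2.6 the drug is given as 40 mg once a day, may be reduced or switched to oral, and is limited to 14 days. Totals of that kind build up in steps and have a ceiling. A treatment that shortens time to response may change their spread as well as their mean. The documents do not show that this will happen.

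**Working it through.** **Inputs from the protocol article.** Mean doses 187.6 and 256.7 mg, SDs 31.1 and 32.9 mg, 87 evaluable per arm (2.5); "we will set α = 0.05 and β = 0.2" (2.5); two-sided tests (2.16); 1:1 allocation (2.1).

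**The plan's own figures.** The plan states no error rate for its rule, so there is none to reproduce. The 87 per arm is used here only as a group size. It does not follow from its own inputs: the pooled SD is √((31.1² + 32.9²)/2) = 32.0, the difference is 256.7 − 187.6 = 69.1 mg, and (1.96 + 0.84)² × 2 × 32.0² / 69.1² ≈ 3.4, that is 4 per group. That is a separate matter and does not affect what follows.

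**Spread in the plan's figures.** SD ratio 32.9/31.1 = 1.06. CVs 31.1/187.6 = 0.17 and 32.9/256.7 = 0.13.

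**Method.** Trials were simulated with equal means in both arms, and the two-sided rejections at 5% were counted. Gamma doses with CV c were drawn with shape 1/c² and scale c² (mean 1, variance c²). Each setting used 4,000 to 20,000 trials.

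| Setting, 87 per arm, equal means | Wilcoxon | Welch |
|---|---|---|
| Normal, the plan's SDs (ratio 1.06) | 5.1% | 5.2% |
| Gamma, the plan's SDs | 5.1% | 5.1% |
| Gamma, the plan's CVs (0.17 v 0.13) | 5.8% | 5.3% |
| Normal, SD ratio 2 (assumed) | 6.0% | 5.0% |
| Normal, SD ratio 3 (assumed) | 7.0% | 5.0% |
| Gamma, CV 0.13 v 0.26 (assumed) | about 9% | about 5% |
| Gamma, CV 0.4 v 0.6 (assumed) | 13 to 15% over separate runs | 5 to 6% |
| Gamma, CV 0.3 v 0.6 (assumed) | 24% | 5% |
| Gamma, CV 0.5 in both arms (assumed) | 5.0% | 5.0% |

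The last row shows that skewness alone does no harm. The excess needs unequal spread.

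**The whole rule, with its pretests.** The plan names no pretests, so Shapiro and Levene tests at 5% were assumed, with the t test used if both pass and Wilcoxon otherwise. The rule rejected 23.7% of the time for CV 0.3 v 0.6, 13.8% for 0.4 v 0.6, 9.1% for 0.13 v 0.26 and 6.0% for normal data with SD ratio 2. Welch gave 4.8%, 5.4%, 4.8% and 5.1%. Whenever the spread differed by 1.5-fold or more, the rule chose Wilcoxon every time, so the pretests give no protection.

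**Is the switch needed?** With 87 per arm the ordinary t test gave 5.0% at normal SD ratios 2 and 3, and 5.2% for gamma CV 0.3 v 0.6. With equal arms it holds its level without any switch. It fails in unbalanced groups, as could arise within an antibiotic subgroup. For 60 v 27 (assumed) with SD ratio 2 and the larger SD in the smaller group, the t test gives 12.1%, Wilcoxon 8.6% and Welch 4.6%. With the larger SD in the larger group the figures are 1.5%, 3.0% and 5.1%. Only Welch stays near 5% both ways.

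**Value of baseline adjustment.** Adjusting for a baseline value that correlates r with the outcome multiplies the residual variance by 1 − r². For assumed r of 0.3, 0.5 and 0.7 this is 0.91, 0.75 and 0.51. The document gives no r.

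**The case against.** The strongest reply is that on the plan's own figures nothing happens: both tests reject about 5 to 6% of the time. That stands, and it limits the size of the point. A second reply also stands. If the granules affect no one, both arms share one dose distribution and Wilcoxon holds 5%. The larger rates describe a treatment that changes the spread but not the mean. The fault is therefore mainly a mismatch between the test and the quantity of interest, not false positives under no effect at all. Third, because mean ± SD is reported, the mg difference can be read off whichever test is used. That is so, but on the Wilcoxon branch the P value does not belong to that difference.

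A separate analysis plan may exist. That does not excuse a rule that the article itself fixes, but it does answer several stronger readings that a reader might draw:

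- *Baseline values are ignored.* Admission CAT is built into the primary endpoint, lung function uses pre-treatment values, and in-trial steroid dose has no natural baseline. An unadjusted comparison of randomised arms is valid; adjustment adds precision.
- *Lung function is analysed only within arms.* The before-and-after sentence stands among the outcome definitions and can be read as timing.
- *Weekly testing makes a false positive likely.* Two scales at 12 weeks would give 1 − 0.95²⁴ = 71%, but only with 24 separate, independent tests. The article plans no such series, and weekly scores from the same patients are not independent. A longitudinal model is something an article may leave to the analysis plan.

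**Conclusion.** The point holds as a fault in the prespecified rule. Unequal variance is sent to a test that does not address it, and the data decide whether the primary test concerns means or ranks. The effect on the error rate is negligible at the SDs the plan assumes. It is appreciable (about 9% to 24% against about 5%) only if the actual doses are skewed with clearly unequal spread, which is an assumption here. The change is worth making because it costs almost nothing and ties the test to the mean dose in mg. Baseline adjustment is a recommended improvement, and its absence is not an error. The documents do not support a claim that the primary test is invalid under the plan's own figures.

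**What to change.** - **Primary analysis.** Replace the conditional rule in 2.16 with one analysis named in advance: the between-arm difference in mean dose, in mg, with a 95% CI. A Welch test is the simplest choice. Linear regression with robust standard errors, adjusted for baseline CAT and baseline FEV1%, also uses data already collected. Choose one and state it.
- **Sensitivity analysis.** Keep Wilcoxon, reported whatever the distribution looks like.
- **Secondary outcomes.** State that lung function, CRP and PCT are compared between arms on the post-treatment value, adjusted for the baseline value. The gain in precision is 1 − r² on the variance, with r unknown.
- **Scope.** The wording must refer to the endpoint as defined in 2.10, the dose at a 50% CAT improvement. This change does not settle what value is analysed for a patient who does not reach that improvement.

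The cost is a few sentences in the protocol or analysis plan and the matching code. No patient, visit or measurement is added.
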